#### Willingness to pay for a BP machine

Assessed using a willingness-to-pay (WTP) questionnaire at 6 months.^28^

#### Extent self-monitoring encourages lifestyle modification

Assessed using the Simple Lifestyle Indicator Questionnaire (SLIQ) score^29^; risk perception score assessed using an adapted questionnaire^30^; the Determinants of Lifestyle Behaviour Questionnaire (DBLQ)^31^; illness perceptions assessed by score on the Illness Perception Questionnaire–Brief^32^; health locus of control assessed by score on the Multidimensional Health Locus of Control (MHLC).^33^

#### Acceptable content and procedures of a future lifestyle component

Assessed using a participant and service provider focus group to discuss the key elements and design of a potential lifestyle component to work alongside SM.

### Procedure

All participants will take part in BP SM and will proceed through the study as outlined in figure 1.

**Figure 1 F1:**
[figure not shown]
Participant flow through the study.

#### Baseline research appointment

Baseline research clinics will be face to-face for individuals identified from GP patient records and online for those identified via a health/BP check or for those identified from GP records who take their own BP at their practice. At the face-to-face appointment, the research team will take the individuals BP. Eligibility criteria will be checked and consent taken from those eligible and willing to participate. Participants will then complete a questionnaire supported by the researcher. Once completed, a date will be set for the online training and a BP machine and study booklet will be given/posted to each participant.

#### Training in SM of BP and study processes

Participants will be trained by the research team to SM their BP, and this will be supplemented with a training video that will be available on the study website. The 1-hour training session will cover how to SM BP, how to record and send readings to the research team, and what actions to take depending on readings. Following the training session, participants will be asked to complete a practice week to ensure confidence and competency with further training offered if required.

#### SM of BP for 6 months

After their training, each participant will start SM at the beginning of the following month. Participants will be asked to SM their BP for 3 consecutive days, starting on the first Monday of each month, for 6 months. The time of day that readings are taken can be decided by the participant but to minimise confounding factors, the time must be kept consistent throughout the 6 months of SM, ensuring they are done no sooner than 30 min after food or exercise and that the timing of medications in relation to readings is kept the same.

Participants will be asked to record two BP readings, along with the time each reading was taken, on each measurement day. They will colour code the second reading on each day as follows:

Green for BPs in the normal range (systolic BP (SBP) <115 AND diastolic BP (DBP) <75 mm Hg),Amber for those in the PHT range (SBP 115–134 OR DBP 75–84 mm Hg),Red for those in the hypertensive range (SBP≥135 OR DBP ≥85 mmHg).

These ranges are based on standard clinical guidelines^1^ but have been reduced by 5/5 mm Hg as recommended for home BP readings. Modified ranges will be provided to relevant participants, for example, the range for those with diabetes will be 10/10 mm Hg lower than guidelines.

After each month’s three measurement days, participants will colour code the overall month as follows:

If there have been any Red days, the month should be classed as Red,If there were no Red days and more Amber than Green days, the month should be Amber,If there were no Red days and more Green than Amber days, the month should be classed as Green.

Red, Amber and Green correspond to hypertensive, PHT and normotensive, respectively. If participants' readings are categorised as hypertensive (Red), over 2 consecutive months, they will send their readings to their GP using a covering letter provided by the research team.

Participants will email, post or telephone their readings, colour coding and actions to the research team each month.

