#### Eligibility criteria

Inclusion criteria: aged 18 years and over; BP in the PHT range (120–139/80–89 mmHg).

Exclusion criteria: current or previous diagnosis of hypertension; prescribed anti-hypertension medication; pregnant; life-limiting illness; history of stroke, heart attack or other significant CVD; being unable to understand verbal and written English.

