#### Protocol adherence

Measured throughout the study, including the number, frequency and timing of self-monitored readings; correct action taken each month; accuracy of recorded readings; reasons for non-adherence.

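### The Amber and Red home-reading bands overlap as written, and no rule says which colour a reading takes when it meets both

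*Protocol article*

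**What the plan says.** The rule is in the protocol article under *SM of BP for 6 months*. Participants measure on three consecutive days a month and take two readings a day. The unit that is coded is a single reading: "They will colour code the second reading on each day as follows". The three bands are:

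- "Green for BPs in the normal range (systolic BP (SBP) <115 AND diastolic BP (DBP) <75 mm Hg")
- "Amber for those in the PHT range (SBP 115–134 OR DBP 75–84 mm Hg")
- "Red for those in the hypertensive range (SBP≥135 OR DBP ≥85 mmHg")

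The limits are said to follow clinical guidelines "but have been reduced by 5/5 mm Hg as recommended for home BP readings". Day colours are then combined into a month colour, beginning with "If there have been any Red days, the month should be classed as Red". If there is no Red day, the majority of Amber or Green days decides. After two Red months in a row, the participant sends the readings to the GP. Each month the participant reports readings, colours and actions to the research team.

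Under *Protocol adherence*, one of the items measured is "correct action taken each month".

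**The concern.** A coding scheme that participants apply on their own should give every reading exactly one colour. Green does this properly, because it joins its two conditions with AND. Amber and Red each join theirs with OR, and nothing in the Amber definition excludes a reading whose other component is in the Red range. Two participants with the same reading could each follow the text and record different colours.

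Three things depend on the result:

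- **The GP-contact step.** Whether two consecutive months count as Red decides whether readings are sent.
- **The adherence outcome.** If a reading has two permissible colours, the text fixes no single correct action, and non-adherence is hard to tell from an ambiguous instruction.
- **Follow-up with practices.** Under *Six-month follow-up appointment*, the team contacts the practices of participants with consecutive Red readings. Who falls in that group depends on the coding.

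**Working it through.** **Inputs.** The clinic range comes from *Eligibility criteria*: "BP in the PHT range (120–139/80–89 mmHg"). The offset and the three bands come from *SM of BP for 6 months*.

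**Step 1: reproduce the plan's limits.** 120 − 5 = 115, 139 − 5 = 134, 80 − 5 = 75, 89 − 5 = 84. The home Amber limits reproduce exactly, so the fault is not in the numbers.

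**Step 2: write the bands as conditions.** With S for systolic and D for diastolic:

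- Green: S < 115 and D < 75
- Amber: 115 ≤ S ≤ 134 or 75 ≤ D ≤ 84
- Red: S ≥ 135 or D ≥ 85

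Amber and Red hold together when (115 ≤ S ≤ 134 and D ≥ 85) or (S ≥ 135 and 75 ≤ D ≤ 84). Green overlaps neither band, and every reading meets at least one.

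| Reading | Amber | Red |
|---|---|---|
| 125/78 | yes | no |
| 140/80 | yes | yes |
| 130/88 | yes | yes |
| 125/88 | yes | yes |
| 140/70 | no | yes |
| 110/88 | no | yes |
| 140/90 | no | yes |

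One oddity shows that the wording is at fault: 140/70 has one colour, while 140/80, with the higher diastolic, has two.

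**Step 3: carry it to the month.** Take days of 140/80, 110/70 and 112/72. The last two are Green. If the first is coded Red, the month is Red. If it is coded Amber, there is no Red day and Green leads 2 to 1, so the month is Green. The month rule cannot choose between these, because it takes the day colour as its input.

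**Step 4: size of the overlap, counting integer pairs.** This needs no distribution, but it depends on the grid chosen.

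- S 90–180, D 50–110. Overlap: 20 × 26 + 46 × 10 = 980. Red: 91 × 61 − 45 × 35 = 5551 − 1575 = 3976. Share: 980/3976 = 24.6%.
- S 100–160, D 60–100. Overlap: 20 × 16 + 26 × 10 = 580. Red: 61 × 41 − 35 × 25 = 2501 − 875 = 1626. Share: 580/1626 = 35.7%.

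**Step 5: size of the overlap under assumed readings.** The article gives no mean, SD or correlation for home readings. The assumptions were bivariate normal readings with means 120/75, 125/78, 130/80 or 135/85, SDs 10/7 or 12/8, and correlation 0.3, 0.5 or 0.7. That makes 24 scenarios, with 400,000 simulated readings in each.

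- Share of Red readings that also meet Amber: 38% to 73%.
- Share of all readings that meet both: about 9% to 38%.

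**Step 6: can one sentence repair it?** As a test of logic only, the overlap was assigned to a single band by limiting Amber to readings that do not meet Red. Every integer pair on S 60–260, D 30–160 then fell in exactly one band, with no gap. Because Green overlaps neither band and no reading is left out, assigning the overlap the other way would also give one colour per reading. Logic therefore does not choose between them, and the trial team must.

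**The case against.** The strongest reply is that the intention can be guessed. The colours form an ordered scale labelled hypertensive, pre-hypertensive and normotensive, and at month level one Red day outweighs the rest. Participants also do not work from the article. They receive a study booklet, an hour of training that covers actions, a video and a practice week, and their competence is recorded. Any of these may contain a tie rule. All of this stands, and it lowers the severity. It does not change the fact that the definitions, which the article gives in full, are not mutually exclusive.

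Three stronger readings are tempting, and the documents do not support them.

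- *Adherence and Red-month rates could not be interpreted.* Raw readings reach the team every month alongside the participant's colours and actions. Once the intended coding is settled, day and month colours can be recomputed for every month reported.
- *A participant following the text would never trigger the GP step.* One day coded Red out of three makes the month Red. A Red-range month is lost only if every Red-range day in it lies in the overlap and each is coded Amber. For the step never to be triggered, this must recur so that no two consecutive months are coded Red. Nothing in the article shows how likely that is.
- *38% to 73% of Red readings would be miscoded.* That range is the share lying in the overlap. A miscoding rate also needs the probability that a trained participant chooses the unintended colour, and the article gives no basis for one.

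The primary outcomes, willingness to engage and acceptability, do not use the colours. What remains is that recomputing colours at analysis cannot recover a letter that was not sent at the time.

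**Conclusion.** The point holds for the rule as written. Amber and Red overlap whenever one component is in the Amber range and the other in the Red range, no precedence is stated for a single reading, and the month rule does not supply one. This follows from the wording alone and needs no assumption.

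Only the extent of the overlap rests on assumptions: 38% to 73% of Red readings under the distributions in step 5. How often participants would in fact code differently cannot be found from the article, and unseen materials may already prevent it. The effect is confined to the GP-contact step, the related check with practices, and one item of a secondary outcome in a descriptive feasibility study. It is a minor to moderate wording correction. It is worth making because participants apply the rule themselves.

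**What to change.** 1. Reconcile the Amber and Red definitions under *SM of BP for 6 months* so that every reading falls in exactly one colour. Which colour the overlapping readings take is for the trial team to settle.
2. Check that the study booklet and training video agree with the reconciled definitions, and correct them if they do not. Check the modified ranges issued to some participants, such as those with diabetes, for the same overlap.
3. For analysis, derive day and month colours by program from the submitted raw readings. Score participants' own coding, and the monthly action item under *Protocol adherence*, against those derived colours.

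The cost is a sentence in the protocol, a check of the participant materials and a short derivation program. No extra data are needed.

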#### Six-month follow-up appointment

After 6 months, all participants will be invited to attend a follow-up appointment and complete an evaluation questionnaire. At the appointment, the research team will audit 2 months (randomly selected) of readings stored on participants BP machines for 20% of the sample. The researcher will also support the participant to complete a second study questionnaire.

Participants will be reminded that in a further 6 months’ time, they will be emailed a link (or posted a paper version) to complete a final questionnaire. They will be informed that there is no expectation for them to continue to self-monitor their BP, but they can do so if they wish. Participants will also be invited to express an interest to take part in an interview and/or a focus group (see Qualitative component section below).

With agreement from participants, the research team will contact the relevant general practice of any participant who has had consecutive Red readings to confirm whether the home readings had been received by the practice.

### Data analysis

#### Quantitative analysis

Data will be exported from the Research Electronic Data Capture (REDCap) into SPSS V.27 (IBM Corporation, LLC) and Stata V.16.1 (StataCorp LLC) for analysis. Descriptive analysis will be conducted for the primary and secondary outcomes. For categorical data, outcomes, proportions and percentages will be calculated. For continuous data, mean and SD, or median and IQR will be used. Secondary outcomes will also be analysed for change over time by using summary statistics and exploratory parametric/non-parametric statistical tests.

Subgroup analyses will be undertaken for gender, age range, BP at baseline, index of deprivation and type of provider. The number of categories for these variables will be determined on clinical and statistical grounds. Parameters instrumental to the power calculations required in any future trial will be investigated.

#### Economic analysis

A cost analysis and a cost-benefit analysis will be undertaken. The cost analysis will quantify the health resource utilisation associated with SM. The resource use information will be determined using:

Self-reported data at baseline, 6 and 12 months on the participants’ health resource utilisation (eg, medications, consultations and referrals due to their PHT) and will be instrumental in estimating any change pre-study and post-study.Data on human resources (eg, training time) employed to set up the SM obtained from the research team at baseline.

Costs will be quantified by multiplying the resource use expressed in natural units by the unit costs drawn from published sources.^34 35^ SM set-up costs will be calculated in the same way. Where standard costs are not available, costs from published works or expert opinion will be used. The cost-benefit analysis will be based on a WTP using an established approach.^28^

Participants will complete a questionnaire at 6 months that captures key factors relevant to buying a BP machine, the maximum price they would be willing to pay and why. The distribution of the WTP values and how they compare against retail prices for similar BP machines will be determined. Regression analyses will identify potential associations between demographic and clinical variables and the WTP values. As part of the WTP analysis, information about the participants’ health-related quality of life will be collected using the EQ-5D-5L^27^ at baseline, 6 months and 12 months to measure change and estimate Quality Adjusted Life Years (QALYs) from baseline to 6 months and from 6 to 12 months.

### Qualitative component

#### Design and methods

The qualitative components of the study will take place between February and September 2023. Up to 35 (20 main study participants; 15 HCPs (pharmacists, pharmacy assistants, GPs, practice nurses and community practitioners) semi-structured interviews will be conducted, as well as a focus group with a subset of 4–8 individuals. The interview questions will be theory-driven (Theoretical Domains Framework (TDF)^36^) and will explore the acceptability of the SM intervention and study processes, including participant and staff experiences of SM, any barriers and facilitators, and ways the study could be improved in future.

The focus group will explore any links between SM and lifestyle changes, what the content and focus of an intervention should look like and how this should be delivered and operationalised in a future trial.

#### Analysis

Qualitative data will be transcribed and analysed using Framework Analysis^36^ and NVivo software to support analysis. Following data familiarisation, analysis will consist of indexing, charting and mapping, and interpretation. The TDF^37^ will be used as a framework for analysis, but any novel emergent themes will be captured and incorporated through an iterative process of constant comparison. This will identify the experiences of, and barriers to, SM.^38^

### Patient and public involvement

Our two patient and public advisors supported the development of all study materials for participants, including posters, letter of invitation, information sheets, consent forms, questionnaires and training video, and will assist in training participants in BP SM. They will contribute to the analysis and preparation of publications to ensure what is produced is meaningful to patients and the public. If this feasibility study supports proceeding to a full trial, our public advisors will contribute to its design and the co-production of the lifestyle intervention to be tested.

### Ethics and dissemination

A favourable opinion for the study has been received from London–Fulham NHS Research Ethics Committee (REF: 22/PR/0108) and the University of Central Lancashire Health Ethics Review Panel (HEALTH 0299) and from the HRA.

We will publish our findings in open-access journals, through a project website and Twitter feed, and feedback to service users and HCPs at professional conferences and training events, public interest groups and charities.

## Discussion

Prevention of CVD is a major priority for the NHS and the single biggest condition where risk reduction strategies including BP reduction can have an impact.^39^ While there is strong evidence for the effectiveness of SM, both on its own and as a co-intervention in reducing BP in hypertension, there is little known about its role in PHT. REVERSE is the first study to assess the feasibility and acceptability of BP SM for people with PHT. With its mixed-methods design, this study will explore whether individuals are able and willing to engage with the concept of PHT and take action to SM their BP, what individual and HCPs’ experiences of SM are, and allow development of a lifestyle component to implement alongside SM.

The study is being conducted in an area which has the highest levels of deprivation, and worst health outcomes in England, and is an area that could benefit the most from this research. The setting of the study reflects recent service model changes, whereby preventative initiatives are moving away solely from general practice and into pharmacy and communities. Utilising settings across primary care also allows people who do not often visit general practice to be reached. This is especially relevant in people with PHT who may not be symptomatic and who are likely to be of working age.

To lessen the time and cost burden for individuals interested in taking part, research clinics will be conducted online where BP has been taken during the identification process, or where BP needs checking for eligibility, the research team will travel to the individual’s general practice. The study will help general practices identify high BP, a key CVD prevention priority. Due to COVID-19, many people have not had their BP checked for a number of years and so with patient permission, high study BP measurements can be provided to GPs for their records and ongoing management.

A limitation of this study is the research team needing to see people for an eligibility BP check. The original design was for all potential participants to be identified via routine health checks across all providers. However, due to the timing of this study in relation to COVID-19, general practices were not offering regular health checks. This has created an extra step in the recruitment process that otherwise would not have been needed.

The main results of this study, expected in April 2024, will inform future research investigating the effectiveness of SM plus lifestyle interventions, in reducing risk of developing hypertension and cardiovascular conditions.
